**E. Procedures**

***Recruitment***

Prior to screening, the study will be explained to all eligible pregnant women and informed consent will be obtained for both the screening procedures, which include testing for HIV, and sickle cell trait, as well as for the SP-folic acid study with three arms (see also annex 2). We will explain to the woman that a decision will be made on whether she can enter the main placebo controlled SP study with three arms after the study physician has reviewed the results of her screening.

Women will be screened at the antenatal clinic at the NPGH, BDH and SDH. A history of previous and present medication use and a medical history will be taken. Body-temperature and weight and height will be recorded. A urine sample will be examined for the presence of sulfa compounds. A blood sample will be obtained by venipuncture to measure hemoglobin, and to make a thick and thin blood smear. In addition, blood will be taken for HIV-tests, electrophoresis to assess the sickle cell status of the woman, and a serum folic acid level. The HIV-status, sickle cell status, and serum folic acid level will only be determined for women who have been enrolled. For logistical reasons it will not be possible to have the sickle cell test result the same day. It is expected that most women with sickle cell disease will not qualify for enrollment because of their medical history and hemoglobin level. Women who have been enrolled but are shown to have sickle cell disease will be informed as soon as the result is available; this will be the day after enrollment or on the first follow up appointment at day 2. They will be removed from the study and provided folic acid supplementation free of charge for one month. The blood requirements for the HIV-tests and the sickle cell test are minimal, and taking this sample when taking blood for screening will save the pregnant woman an additional venipuncture if she is enrolled.

Before the woman is enrolled, she will be counseled by the Prevention-of-Mother-to-Child-Transmission-of-HIV program in the antenatal clinic. . Post-test counseling will be done by the PMCT program in the prenatal clinic, and supportive counseling will be offered. Because the HIV counseling and testing for the ANC is confidential, a request for the HIV test result of the HIV tests done in the ANC could harm the thrust build up among counselors and ANC-attendees. HIV tests will be repeated by the study laboratory by code, and participants will be informed about the result of the second HIV tests by the study counselor or study nurse during the first follow up appointment on a weekday, and ongoing counseling will be provided. Women who claim that the HIV results of the study are different from the results in the ANC will be offered a Western blot test and a follow up appointment with the study counselor or study nurse about the result.

Decisions on enrollment in any of the three arms will be made by the study physician according to the inclusion and exclusion criteria listed. When the hemoglobin level and the blood-smear result are available to the study physician, and enrollment criteria have been met, the woman will then be allocated to one of the three treatment regimen: SP once and daily folic acid 5 mg, SP once and daily folic acid 400 g for 14 days, or SP once and folic acid placebo for 14 days. Both client and researcher will be blind to the allocation. The intake of SP and the first dose of folic acid 500 mg, folic acid 400 g or folic acid placebo will be supervised in the study clinic. The folic acid 500 mg, folic acid 400 g and the folic acid placebo will be dispensed in a quantity of 14 tablets. Women will be asked to bring the medication whenever they visit the study clinic, to facilitate tablet counts. An address form will be completed to allow the study team to do home visits if a woman does not turn up for her follow up appointment.

Women who are enrolled will be instructed to take the folic acid 400 g, folic acid 5 mg or placebo daily and to come to the clinic if they feel they need medication other than the study medication. All participants will receive iron supplementation as well (ferrous sulphate 200 mg three times per day, clinical guidelines of the Ministry of Health, Kenya). Clients will be specifically asked not to self-administer antimalarials or other drugs, vitamins or minerals during the period of follow up and to return to the study team if they should develop fever, jaundice, skin rash or any complaint for which they might need medical treatment.

After randomization, the study will provide insecticide-treated bed nets to all enrolled women. The rationale for their use is that they reduce the chances of reinfection of enrolled women. This makes is more likely that a recurrence of parasitemia is a recrudescence rather than a reinfection, whereby a recrudescence would be an indication of treatment failure, and a reinfection would not. In addition, several studies, including one recently completed in western Kenya, indicate that insecticide-treated nets confer benefits to women and their neonates; they were associated with reductions in maternal anemia and parasitemia, and an improvement in infant birth weight (Ter Kuile et al, 2003). Women will be informed about the importance of the personal use of a bed net and instructed on how to use the bed net properly.

***Malaria:*** To identify malaria, a thick and thin smear obtained by venipuncture from the women screened or by finger stick from the women who have been enrolled will be stained with Giemsa and examined microscopically.

***HIV-testing:*** HIV-testing will be performed using the test Determine HIV-1/2 (Abott Laboratories, Dainabot Co. Ltd, Tokyo, Japan) and Unigold HIV (for HIV-1 & HIV-2, Trinity Biotech plc, Bray, Ireland), in case of an inconclusive result the rapid test Capillus HIV-1/HIV-2 (Cambridge Diagnostics, Wicklow, Ireland) will be used. These tests are used by the CDC Global Aids Program in the antenatal clinic and for voluntary testing and counseling in the same hospital. If HIV tests results between the ANC and the study tests differ according to the client, the client will be offered a Western Blot test.

***Hemoglobin:*** Hemoglobin will be measured using a Hemocue® hemoglobin detection system (HemoCue AB, Angelholm, Sweden).

***Sickle cell status:*** The HbS genotype of the enrolled women will be assessed using electrophoresis of a red blood cell haemolysate on cellulose acetate plates (Helena

laboratories, USA). Samples will be collected in EDTA microtainers and stored at 4 "C before testing.

***Sulfa-test urine:*** The method of Mount et al (1996), will be used to test the urine for sulfa compounds. In case of a positive urine test for sulfa-compounds the woman will be excluded from the study.

***Follow up:*** Women will be asked to return on day 2, day 3, day 7, day 14, day 21, and day 28 (see annex 2). At these days the malaria smear will be repeated, and women will be questioned on complaints, side effects and medication use. They will be asked to bring the folic acid tablets (either folic acid 400 g, folic acid 5 mg or folic acid placebo) that are remaining to every clinic visit and a tablet count will be done to ensure compliance. Blood will be taken by finger stick for a malaria smear at every follow up date and in case of intercurrent visits. On day 2 or the first follow-up appointment made on a weekday, all clients will see the study counselor or study nurse to be informed about the HIV-test results of the study. At day 7 an additional 1 ml of blood will be taken for serum folate levels to assess adherence. At day 14 and 28, a hemoglobin measurement will be done. Women who do not return for follow up sampling will be visited at home to ask if they are still interested in participating. They will be encouraged to visit the clinic, or blood samples will be taken at home. If a woman develops early or late treatment failure or shows failure to clear parasites during follow up at day 7, day 14, or day 21, she will be treated with quinine, 600 mg three times daily for 7 days, according to the national guidelines. If a woman is parasitemic on day 28, she will receive her next dose of intermittent presumptive treatment with SP if there are no contra-indications (no history of side-effects), otherwise she will also receive quinine. During enrollment, the importance of ensuring their parasitemia is cleared with the alternative drug (quinine) and the need to adhere to their dosing regimen will be emphasized to women. In addition, they will be advised that quinine in therapeutic doses is felt to be safe to take during pregnancy. They will be informed about the potential side-effects of quinine, and advised that these side effects though unpleasant are almost always reversible. Thus, they will be told to continue the medication despite side effects but told to return to clinic for further consultation if they experience serious side effects or if they feel they cannot tolerate the side effects. Women who have a treatment failure on SP and who are treated with quinine will receive a follow-up appointment after 7 days to ensure clearance of parasitemia. Women who have parasitemia on day 7 after the initiation of quinine for SP treatment failure will be offered admission for supervised quinine intake, paid by the SP-folate study (because of the side-effects, many women may not adhere to quinine). Women who refuse admission for supervised quinine therapy will be offered the option of mefloquine treatment. A follow-up appointment after 1 week will be made to ensure clearance of parasitemia after either supervised quinine therapy or mefloquine therapy. If women do not show up for their post-treatment failure visits, they will be visited at home. Mefloquine is mentioned as an alternative drug that can be used for the treatment of malaria in pregnancy in the “Clinical guidelines for diagnosis and treatment of common conditions”, published by the government of Kenya (MOH Kenya 2002).

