***Criteria for inclusion***

1. Parasitemia with a parasite density of ≥ 500 parasites/microliter
2. Gestational age > 16 weeks and < 35 weeks
3. Willingness to provide blood samples and participate in HIV counseling and testing
4. Available for follow up for the entire study period
5. Hb > 7 g/dl
6. Age 15-45 years

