**D. Outcome measures and sample size**

Outcome measures in the three arms will be the prevalence of parasitemia at day 2, 3, 7, 14, 21 and 28 following treatment with SP and change in hemoglobin level comparing day 0 (day of SP treatment) to day 28. In line with international criteria the following definitions are used (WHO 2003, see also Annex 5). Early Clinical Treatment Failure (ETF) will be defined as having at least one of the following: (a) the development of danger signs of severe malaria (see above under exclusion criteria 9) on day 1, 2, or 3 in the presence of parasitemia; (b) parasitemia on day 2 higher than the day 0 count; (c) parasitemia on day 3 in the presence of an axillary temperature of ≥ 37.5; or (d) parasitemia on day 3 ≥ 25% of the parasite count on day 0. Late Clinical Treatment Failure (LTF) will be defined as either the presence of parasitemia on any day from day 4 to 28 in the presence of an axillary temperature of ≥ 37.5, OR the development of danger signs after day 3, without previously meeting any of the criteria of ETF. Late parasitological failure is defined as the presence of parasitemia on any day from day 7 to 28, in the presence of an axillary temperature of < 37.5 without previously meeting any of the criteria of ETF or LTF.

A sample size of 600 women, 200 of whom receive SP and folic acid 5 mg, 200 of whom receive SP and folic acid 400 g and 200 of whom will receive SP and placebo folic acid for 2 weeks, will allow us to detect an increase from 5% to 15% parasitological failure rate at day 7, comparing the folic acid placebo arm with the folic acid 5 mg arm and the folic acid 400 g arm, with 80% power and 95% confidence, when taking 25% loss to follow up into account.

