There are no indications from the previous studies in pregnant women in Malawi and Kenya that intermittent use of SP treatment doses (once per trimester or once monthly) was associated with severe skin reactions as has been reported for weekly prophylactic use (Parise et al, 1998, Verhoeff et al, 1998). The Kenyan guidelines for IPT will be followed, excluding the delivery of SP to pregnant women in their first trimester, and thus the potential teratogenic effect of pyrimethamine and sulfadoxine, and excluding the delivery of SP to women after 34 weeks of gestational age, and thus the theoretical risk of kern-icterus in the newborn in association with sulphonamides (Phillips-Howard & Wood, 1996).

Pregnant women identified with sickle cell disease who have been enrolled in the study will be contacted as soon as possible, either before or at their scheduled appointment on day 2. They will be provided with folic acid and excluded from the study. If they have been enrolled in the “no-folate” arm of the study, this means there will be a delay of one or two days before they start on folic acid. We do not expect that the deprivation of folic acid for one or two days will have serious detrimental effects on their health. However, we anticipate that, given the range of complaints associated with sickle cell disease in this environment and the likelihood of anemia, most women with sickle cell disease will have been excluded from participating in this study during the screening phase.

Pregnant women who do not want to participate in the study, will receive the two-dose regimen of SP, and will be given folic acid tablets free of charge in the ANC provided by the Ministry of Health.

Women with a treatment failure to SP will be treated with quinine and followed after 1 week to ensure clearance of the parasitemia. Women who do not clear their parasitemia will be offered admission for daily supervised quinine treatment free of charge. Women who refuse admission will be given the option of taking mefloquine after an explanation of potential risks and benefits. All women with parasitemia after quinine treatment will get a follow up appointment 1 week after the alternative treatment until their parasitemia has cleared.

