The most common side effects reported with quinine therapy include dizziness, decreased hearing, tinnitus, blurred or double vision, photophobia, nausea, and vomiting. Although the US drug labeling categorizes quinine (Merrell Dow) as Category X (contraindicated), the congenital abnormalities reported occurred at abortifacent doses (Briggs et al, 1986). In addition, quinine at therapeutic doses is not felt to induce premature delivery (Looareesuwan et al, 1985). Quinine is recommended as the drug of choice for treatment of uncomplicated and severe malaria during pregnancy, including CDC (http://www.cdc.gov/malaria/diagnosis_treatment/clinicians3.htm), Health Canada (CATMAT: http://www.hc.sc.gc.ca/pphb-dgspsp/publicat.htm) and the WHO (WHO 2001).

The most common potential adverse drug reactions associated with mefloquine include headache, nausea, dizziness, difficulty sleeping, anxiety, vivid dreams, and visual disturbances. Mefloquine treatment can also cause serious side effects, such as seizures, depression, and psychosis. Mefloquine has not been shown to be associated with congenital abnormalities (Phillips-Howard & Wood, 1996; McGready et al 2002). However, one retrospective study from Thailand reported that mefloquine treatment may be associated with an increased rate of stillbirths but no definite conclusions could be drawn (WHO 2001, Nosten et al 1994, 1999). Given this uncertainty, we feel that mefloquine should be used only for women who fail quinine therapy (or who cannot tolerate it). Because malaria can have severe adverse consequences for both mother and fetus, women need treatment for parasitemia during pregnancy and we feel that in women who have failed quinine (who have no other better option), the benefits of mefloquine therapy outweigh the risks. WHO has recommended that mefloquine can be used for treatment of malaria during pregnancy in the 2nd and 3rd trimesters (WHO 2001).

Although amodiaquine is regularly used in Kenya for malaria in pregnancy, and is mentioned as well as a treatment option in the national guidelines (MOH 2002), a recent review exposed the lack of safety data on amodiaquine in pregnancy (Thomas et al, 2004), and for this reason we do not feel it is a good option for treatment of SP treatment failure.

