Annex 2: Follow up schedule for participating pregnant women

| Day | Action | Form | Laboratory |
| --- | --- | --- | --- |
| 0 | a) Screening  b) Enrollment  c) Randomization  d) Supervised SP  e) Instruction and supply of folic acid/placebo tablets, supervised first dose  f) Supply of iron tablets 60 mg/day | Screening form  Enrollment form | Thin and thick blood smear  Hemoglobin  HIV-testing  Sickle cell test  Filter paper sample for PCR  Urine for sulfa test |
| 2 | a) Follow up,  b) Supervised folic acid/placebo | Follow up form | Thin and thick smear |
| 3 | a) Follow up  b) Supervised folic acid/placebo | Follow up form | Thin and thick smear |
| 7 | a) Follow up  b) Supervised folic acid/placebo | Follow up form | Thin and thick smear |
| 14 | a) Follow up  b) New supply folic acid tablets for all women | Follow up form | Thin and thick smear  Hemoglobin |
| 21 | a) Follow up  b) Supervised folic acid | Follow up form | Thin and thick smear  Filter paper sample for PCR |
| 28 | a) Follow up  b) New supply folic acid /iron | Follow up form | Thin and thick smear  Hemoglobin |
| x | Intercurrent visit: visit in between follow up visits | Follow up form | Thin and thick smear  Hemoglobin |

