**______________________________________________________________________________**

**14.** Conclusion: [_] 1) Continue, next appointment: [_][_]/[_][_]/[_][_]

2) Excluded: reason: [_]

3) Dropped out: reason:

4) End of study after 28 days

Reasons for exclusion:

1. Use of other sulfa containing drugs or antimalarials when being in the study.

2. RIII resistance: -A parasite density at Day 3 that is > 25% of the Day 0 parasite density.

3. RII resistance: -Parasites at 7 days and a positive blood smear at day 3 with a parasite density that is < 25% of the Day 0 parasite density.

4. Early RI: -A negative Day 3 blood smear with a positive blood smear on any day between Day 4 and Day 14 or a positive Day 3 blood smear with a parasite density that is < 25% of Day 0, a negative Day 7 blood smear, and a positive blood smear on any day between Day 8 and Day 14.

5. Sensitive or late RI: -A Day 3 parasite density that is <25% of the Day 0 density and negative blood smears on every follow-up examination between Day 7 and Day 14.

6. Other reason, specify_________________________________________________

**In case of clinical or parasitologic failure: treat with Quinine 600 mg TDS for 7 days, and make a new appointment after 7 days.**

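### Women found to have sickle cell disease are removed on day 1 or 2 after SP for confirmed parasitaemia, with no later smear or rescue visit written for them (minor safety point)

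*Protocol*

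**What the plan says.** Section VII.C requires "Parasitemia with a parasite density of ≥ 500 parasites/microliter" for entry and lists sickle cell disease as an exclusion. Section VII.E (Recruitment) explains that the sickle cell result cannot be had on the day of screening. A woman with the disease may therefore be enrolled, take SP under supervision on day 0 and start study tablets. She learns the result the next day or at the day 2 visit.

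For these women section VII.E states: "They will be removed from the study and provided folic acid supplementation free of charge for one month". Section VIII.E gives the same rule: "They will be provided with folic acid and excluded from the study". Neither section mentions a further smear.

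Malaria follow-up is described in section VII.E (Follow up): smears on days 2, 3, 7, 14, 21 and 28, home visits for missed appointments, and quinine, with mefloquine in reserve. Rescue applies on early or late treatment failure, or if a woman "shows failure to clear parasites during follow up at day 7, day 14, or day 21". Annex 2 is titled "Follow up schedule for participating pregnant women". In section VII.D, "Late parasitological failure is defined as the presence of parasitemia on any day from day 7 to 28", in the absence of fever.

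**The concern.** The study itself has found the woman parasitaemic and treated her. If the removal rule is followed as written, nobody is told to check whether the treatment worked.

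She also starts, or continues, folic acid within a day or two of SP, which is the exposure the trial suspects of weakening SP. Section IV cites a WHO recommendation to delay folic acid for a week after SP, and section V doubts that the national two-day delay is long enough. Section VIII.E accepts that women given folate in the study may be at higher risk of treatment failure and promises that they will be followed closely. The removal rule takes a woman with a similar exposure out of that follow-up. The same section also says: "Because malaria can have severe adverse consequences for both mother and fetus, women need treatment for parasitemia during pregnancy".

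What is at stake is the welfare of a few participants, namely persistent parasitaemia without fever that no scheduled smear would find. The trial's result is not at stake.

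**Working it through.** **1. What removal on day 1 or 2 leaves unchecked** (sections VII.D and VII.E, Annex 5)

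| Day | What the planned check detects | Told on day 1 | Told at day 2 visit |
|---|---|---|---|
| 2 | Count above day 0, or danger signs with parasitaemia | Not assured | Read |
| 3 | Count at least 25% of day 0; any parasitaemia with fever; danger signs with parasitaemia | Not written | Not written |
| 7, 14, 21 | Any parasitaemia, with or without fever; quinine | Not written | Not written |
| 28 | Any parasitaemia; next SP dose or quinine | Not written | Not written |

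Each woman loses at least five scheduled smears (days 3, 7, 14, 21, 28), four of them from day 7.

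**2. Is another check written elsewhere?** Section VIII.D offers a consultation with a sickle cell specialist, and free malaria treatment to participants during the study period. Section VII.E gives a bed net and advice to return if unwell. None of these schedules a smear, and the advice depends on symptoms. By contrast, women who fail SP get an explicit check visit after one week (sections VII.E and VIII.E, Annexes 4 and 5).

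**3. How many women**
- Upper bound: section IV gives a prevalence under 1% in children in an adjacent area; 600 × 0.01 = 6, so fewer than 6.
- Assumed: 0 to 3, because section VII.E expects most cases to be screened out by history and haemoglobin.
- Chance of at least one case, 1 − (1 − p)^600: 45% at p = 0.1% (0.6 expected), 95% at 0.5% (3 expected) and 99.8% at 1% (6 expected). These values of p are assumptions.

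**4. How many missed failures**
- At the section VII.D design rates for day 7: 3 × 0.05 = 0.15 to 3 × 0.15 = 0.45; at the upper bound, under 6 × 0.15 = 0.90.
- To day 28 the protocol gives no design rate. For illustration only, the Gambian children described in section IV had cumulative failure of 16.0% without folic acid and 30.1% with it: 3 × 0.160 = 0.48 to 3 × 0.301 = 0.90; at the upper bound, under 6 × 0.301 = 1.8.

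**5. Smears kept by the remedy**
- Days 3 and 7 only: 3 × 2 = 6 (under 12 at the upper bound).
- Day 3 to day 28: 3 × 5 = 15 (under 30).
- Already planned: 600 × 6 = 3,600.

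**6. Power.** The plan's 200 per arm is reproduced: 5% against 15%, two-sided 5% level, 80% power, with continuity correction, needs 160 per arm, and 160 × 1.25 = 200. With 25% lost, 200 × 0.75 = 150 remain. Power by the pooled normal approximation without correction is 82.6% at 150 per arm, 82.4% at 149 (three women spread over three arms) and 82.1% at 148 (six women). The loss is immaterial.

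**The case against.** The strongest objection is that the harm is read into silence. The protocol says these women leave the study; it never says that smears or malaria care stop. That is correct, and a reader who infers that the protocol orders care to end goes beyond the text. What remains is narrower: the visits and rescue are written for women in follow-up, these women no longer are, and nothing replaces what they lose.

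A reader might also cite the follow-up form in Annex 4, where the option "Continue, next appointment" carries a date and the exclusion option does not. That does not show that follow-up ends. The form also classes SP failures as exclusions, and those women get a new appointment after seven days. Exclusion there does not mean the end of malaria care.

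Nor is the day 2 visit limited to a rising count. Danger signs with parasitaemia on days 1 to 3 also count as failure.

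Other women get no clearance smear either. For those who decline, the comparison is weak: consent precedes screening, so the study has not found them parasitaemic. It is fairer for women who are smear-positive but ineligible, for example with a density below 500. The removed woman still differs, because the study has given her SP, has started or continued folic acid soon afterwards, and already has her visits planned.

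She has also had a full supervised SP dose and remains an antenatal attendee who may receive a second SP dose at 28 to 34 weeks. These facts lower the risk, but they do not check clearance and may not help a woman enrolled late in that window.

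Finally, very few women are involved. That stands, and it sets the weight of the point.

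**Conclusion.** The point holds as a minor safety improvement. Sections VII.E and VIII.E remove a woman known to be parasitaemic one or two days after SP and start folic acid, and no section gives her a later smear or rescue visit. The day 3 criterion and afebrile parasitaemia from day 7 then go unchecked.

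The conclusion rests on an inference from the Follow up text and Annex 2. It also rests on an assumed 0 to 3 affected women, bounded at fewer than 6 by a prevalence in children. At the day 7 design rates this is less than one missed failure even at the upper bound.

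Two stronger readings are not supported. Giving folic acid is not an error, since section IV says women with known sickle cell disease should receive it. And the removals do not threaten power or bias the efficacy comparison to any material degree.

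**What to change.** Add one sentence to section VII.E (Recruitment) and one to section VIII.E: women removed for sickle cell disease stop study tablets, start folic acid and leave the efficacy analysis, but for safety keep the malaria smear visits already planned, with the same home visits and quinine/mefloquine rescue. The minimum is smears on days 3 and 7. Visits to day 28 are preferable, because late failure is defined to day 28.

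No new procedure is needed. The minimum keeps 0 to 6 smears (fewer than 12 at the upper bound) and the full option 0 to 15 (fewer than 30), out of 3,600 already planned. The downside is a few extra visits for these women.

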**Late clinical failure**:

- Development of danger signs of severe malaria after day 3 in the presence of parasitemia without previously meeting any of the criteria of *Early Treatment Failure*
- Presence of parasitemia and an axillary temperature ≥ 37.5 ºC on any day from day 4 to 28 without previously meeting any of the criteria of *Early Treatment Failure*

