**Late parasitological failure**:

- Presence of parasitemia on any day from day 7 to 28 and an axillary temperature of < 37.5 ºC without previously meeting any of the criteria of *Early Treatment Failure* or *Late Clinical Failure*

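### The protocol gives opposite treatment instructions for a woman parasitaemic on day 28, and schedules no clearance check if she is given SP

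*Protocol*

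**What the plan says.** **Treatment rule in the body (Protocol VII.E, Follow up).** Quinine, 600 mg three times daily for 7 days, is triggered as follows: "If a woman develops early or late treatment failure or shows failure to clear parasites" at the day 7, 14 or 21 visit. Day 28 has its own rule: "If a woman is parasitemic on day 28, she will receive her next dose of intermittent presumptive treatment with SP". The condition attached to that dose reads: "if there are no contra-indications (no history of side-effects), otherwise she will also receive quinine". The clearance visit is then set by drug: "Women who have a treatment failure on SP and who are treated with quinine will receive a follow-up appointment after 7 days". Later checks in that paragraph follow supervised quinine or mefloquine.

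**Failure definitions (Protocol VII.D and Annex 5).** Late clinical failure covers "presence of parasitemia on any day from day 4 to 28 in the presence of an axillary temperature" at or above the fever threshold. Annex 5 gives the same window, "on any day from day 4 to 28 without previously meeting any of the criteria of" early treatment failure. Late parasitological failure in Annex 5 is "Presence of parasitemia on any day from day 7 to 28" without fever, in a woman who has not already failed. Both windows include day 28.

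**Working tools.** The Annex 5 staff sheet is to be placed in each participant file. It has a single row for days 7 to 28: any parasitaemia, with or without fever or danger signs, is a treatment failure. Its closing line directs quinine and a check one week later. The follow-up form (SPF-FORM 2) ends with an instruction to treat clinical or parasitologic failure with the 7-day quinine course and to book an appointment after 7 days.

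**The concern.** A woman whose smear first turns positive on day 28 is covered by two rules that name different drugs. The body text repeats the drug that, by the protocol's own definition, has just failed. The sheet in her file changes the drug. Because the clearance visit is attached to quinine, the choice of drug also decides whether anyone is scheduled to confirm that her parasites have cleared.

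What is at stake is the care of a pregnant woman with parasitaemia and uniform conduct across three hospitals. A woman found positive one week earlier, on day 21, would receive quinine and a check under every version of the rule.

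**Working it through.** No arithmetic bears on this point beyond dating the check visit. The test is to follow one case through each text: a woman smear-negative on days 7, 14 and 21, smear-positive on day 28, without fever or danger signs, and with no past side effects from SP.

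1. **Is she a failure by definition?** Yes. Day 28 lies inside the late parasitological window in VII.D and Annex 5.
2. **VII.E, Follow up.** The quinine sentence names days 7, 14 and 21, so the day-28 sentence applies: SP. The 7-day clearance visit is stated for women treated with quinine. None is stated for her.
3. **Annex 5 staff sheet.** Day 28 is inside the 7-28 row. She is a treatment failure, gets quinine and is checked after one week (day 28 + 7 = day 35). The sheet makes no exception.
4. **Follow-up form.** Its closing instruction covers parasitologic failure and does not name day 28. Read with the definition in step 1, it gives quinine and an appointment after 7 days. This is one step of inference, whereas step 3 is explicit.

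| Text | Drug on day 28 | Clearance check stated |
|---|---|---|
| VII.E, Follow up | SP (quinine if SP contra-indicated) | Only after quinine |
| Annex 5 staff sheet, days 7-28 | Quinine | Yes, one week |
| SPF-FORM 2, read with VII.D and Annex 5 | Quinine | Yes, 7 days |

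If SP is contra-indicated, all three texts give quinine, so the clash is confined to women without a contra-indication. They are the default case.

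**Effect on the results.** The day-28 smear is read before this treatment is given, and the last scheduled haemoglobin is also taken on day 28. The choice of rescue drug cannot change the day-28 outcome data.

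**The case against.** The best defence is that the day-28 rule is deliberate. VII.E lists days 7, 14 and 21, then gives day 28 its own sentence and its own quinine fallback. A woman who attended every visit and reached day 28 was smear-negative at the three preceding weekly visits, so reinfection is possible. The bed-net paragraph of VII.E says that a reinfection would not indicate treatment failure. SP is a supervised single dose, whereas VII.E says of quinine: "because of the side-effects, many women may not adhere to quinine". This stands as a reason not to assume that the SP rule is a mistake. It does not remove the clash, because the sheet and the form carry no exception. If SP was intended, those two are wrong.

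A reader might also infer more than the text supports:

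- **That VII.E contradicts itself for a febrile woman.** A natural reading is that the quinine sentence already covers clinical failures on any day, and the day-28 sentence covers what is left. On that reading there is no internal conflict.
- **That the risks section (VIII.E) is a further text requiring quinine on day 28.** It prescribes quinine for treatment failure. VII.D keeps that term for early and late clinical failure and names parasitological failure separately, while the heading of Annex 5 groups all three. For an afebrile woman VIII.E is ambiguous, so counting texts for and against adds nothing.
- **That SP on day 28 has no gestational limit.** VIII.E says the national IPT guidelines will be followed and excludes SP after 34 weeks. That limit applies across the trial.
- **That folic acid is to be taken with the day-28 SP dose.** VII.E does not address folate timing for this dose. That is silence, not an instruction.
- **That ending follow-up at day 28 (VII.B) is what removes the check after SP.** VII.B ends routine follow-up for everyone, including women given quinine on day 28. The gap rests on VII.E alone.

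**Conclusion.** The point holds. For a woman parasitaemic on day 28 without a contra-indication to SP, the body of the protocol directs SP, while the sheet in her file directs quinine and a one-week check. The follow-up form agrees with the sheet once the failure definition is applied. On the SP branch no clearance check is scheduled for a woman who meets the protocol's definition of failure.

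This is a minor reconciliation of safety and conduct. No endpoint, treatment comparison or power figure changes. The number of women affected cannot be derived from the protocol. The staff sheet already points to quinine and a check, which limits the practical risk if staff work from it.

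The conclusion assumes that the sheet and form were used as printed, and that parasitologic failure on the form has the meaning given in VII.D and Annex 5. It does not extend to saying that SP on day 28 is the wrong drug. That is a clinical trade-off which the documents do not settle.

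**What to change.** Make the three texts agree, in one of two ways.

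- **Quinine on day 28.** Replace the day-28 sentence in VII.E with a statement that a woman parasitaemic on day 28 is managed as on days 7 to 21: the 7-day quinine course and a clearance appointment after 7 days. The sheet and form then need no change.
- **SP on day 28, if that is the intention.** Keep the sentence and add a matching day-28 exception to the Annex 5 sheet and to SPF-FORM 2. Limit it to afebrile women without danger signs and to gestation of 34 weeks or less, the limit already in VIII.E. All others get quinine.

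In either case, state in VII.E that the one-week clearance check follows whichever drug is given.

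The cost is a sentence or a few lines of text and one extra visit around day 35 for the women concerned. Choosing quinine adds its side effects and the adherence problem, with supervised quinine or mefloquine if parasites persist. The protocol already accepts these burdens for failures up to day 21.
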